**Data collection and measures**

A standardised battery of measures will be completed at baseline, three, six and 12 month follow up, except for weight and the King’s Obesity Staging Criteria which will be collected at baseline and 12 month follow up only to allow for meaningful change. Demographic data: self-reported medical history, age, gender, work status, educational level, ethnicity, marital status, number of dependents, current or past psychological therapy and current medications, will also be collected at baseline. Baseline and 12 month follow up data will be collected face to face to coincide with routine clinic appointments; three and six month follow up data will be collected via telephone.

*Primary outcome measures*

The primary outcome is the feasibility of the trial methodology. This will be measured by, (1) The willingness of participants to be randomised, measured by recording the number of participants who drop out of the study after they have been randomised, (2) the number of eligible patients attending clinic, as assessed by calculating the percentage of patients who meet eligibility criteria at screening, (3) follow-up rates, assessed by the percentage of participants retained until 12 month follow-up and providing complete datasets, (4) adherence to the intervention or control, assessed by number of sessions attended, (5) reasons for attrition, (6) the time needed to collect data and (7) the acceptability of the intervention at 12 month follow-up, as assessed by a 5 point likert scale (1=“Not at all”, 3=“somewhat”, 5=“Very”) to evaluate how helpful participants found the treatment, their satisfaction with it, and how likely they would be to recommend it to a friend and (8) the standard deviation of weight maintenance (<5% weight gain from baseline assessment) or weight loss, in order to estimate the required sample size for a future trial (measured at study close-out).

*Secondary outcome measures*

Outcomes relating to (A) obesity, health and wellbeing, (B) costs, and (C) measures of ACT processes will be collected to test the appropriateness and acceptability of measurement instruments to be used as outcomes in a full trial. The validated instruments to be used are listed below.

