### *Obesity and health and wellbeing*

The King's Obesity Staging Criteria. This measures the severity of an individual's obesity based on a four-graded set of health-related domains. It can capture health problems related to obesity and health benefits after weight loss.

The International Physical Activity Questionnaire (IPAQ). This measures levels of physical activity.

The Brief Mediterranean Diet Questionnaire. This measures adherence to a Mediterranean diet which is recommended as part of the intervention.

The Alcohol Use Disorders Identification Test (AUDIT). This measures alcohol consumption, drinking behaviours, and alcohol-related problems.

The Dutch Eating Behaviour Questionnaire (DEBQ). This measures eating behaviour in terms of restraint, emotional, and external eating.

The Hospital Anxiety and Depression Scale (HADS). This measures levels of anxiety and depression.

Weight in kilograms.

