### *Costs*

The Client Service Receipt Inventory (CSRI). This measures resource use by participants by asking them about their health service use and social service over the last 3 months. Questions relate to healthcare use in both primary care [general practitioner (GP) and community nursing services] and secondary care as well as accident and emergency (A&E) department. Participants will be asked to report the frequency and intensity of their service use.

EQ-5D-5L: This measures health-related quality adjusted life years (QALY). The five attributes of this questionnaire (mobility, self-care, usual activities,

pain/discomfort/anxiety/depression) will be summarised into a single UK-derived preference-based utility score.

ICECAP-A (ICEpop CAPability measure for Adults): This is a measure of capability for the general adult population for use in economic evaluation. It focuses on wellbeing defined in a broader sense than health. The measure covers attributes of wellbeing that were found to be important to adults in the UK.

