#### *ACT processes*

The Distress Tolerance Scale (DTS). This measures ability to tolerate distress.

The Philadelphia Mindfulness Scale (PHLMS). This measures present moment awareness and acceptance.

The Drexel Defusion Scale (DDS). This measures cognitive distancing or 'defusion'.

The Physical Activity Acceptance Questionnaire (PAAQ). This measures the extent to which an individual is able to tolerate physical or psychological discomfort.

The Food Acceptance and Awareness Questionnaire (FAAQ). This measures acceptance of food-related thoughts and urges.

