#### *Statistical data analysis*

Analyses will be undertaken using R program. All significance tests will be 2-tailed and alpha will be set at  $p < 0.05$ . The distribution of the study population will be characterised using descriptive summary statistic parameters, that is median, range, mean, and standard deviation. Then, we propose to use ANCOVA to calculate variations within primary and secondary outcome measures pre-treatment and at follow-up. Anonymised data from those who decline to participate will also be reported. Complete case analysis and intent-to-treat analyses (using last measurement carried forward for participants who provided baseline assessment measurements) will be conducted.

A cost-consequence analysis (CCA) will be carried out from a National Health Service (NHS) perspective. This involves listing the costs and outcomes associated with ACT and the Usual Care Support Group separately, allowing decision-makers to compare the relative value of approaches, and by calculating resource use. The intervention costs will be calculated based on the activities involved in delivering the programme such as staff salaries, administrative and managerial costs.

Total costs of the individuals in the two groups will be compared and estimated by multiplying the resource use with the unit costs of health and social care. We will present the additional costs associated with the intervention and present the costs alongside the benefits (if any) identified in the trial. Sensitivity analyses to model uncertainties around all key cost and outcome parameters, and plausible ranges will be specified using information from the trial and from the literature specific to the population in the study will be conducted.

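### The secondary measures are collected to judge the instruments, but the inferential analysis named for them tests scores, and no instrument-level assessment is planned

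*Protocol*

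**What the plan says.** **Purpose.** Under Secondary outcome measures (Protocol, Data collection and measures), the outcomes on obesity and health, costs and ACT processes "will be collected to test the appropriateness and acceptability of measurement instruments to be used as outcomes in a full trial". The Abstract makes a matching promise: the trial is to report on the properties of the proposed outcome measures for a definitive trial.

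**Schedule.** The battery is given at baseline and at 3, 6 and 12 months. Weight and King's staging are taken at baseline and 12 months only. Baseline and 12 months are face to face; 3 and 6 months are by telephone.

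**Analysis.** In Statistical data analysis, "we propose to use ANCOVA to calculate variations within primary and secondary outcome measures pre-treatment and at follow-up", with two-tailed tests at 0.05. The same section adds three other elements:
- Summaries of the sample: "The distribution of the study population will be characterised using descriptive summary statistic parameters, that is median, range, mean, and standard deviation".
- Two ways of dealing with missing values: "Complete case analysis and intent-to-treat analyses (using last measurement carried forward for participants who provided baseline assessment measurements) will be conducted".
- An economic analysis that sets costs beside consequences by arm, taken from the NHS point of view.

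The Sample size section says that hypotheses will not be tested and gives this as the reason for having no power calculation.

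**Related feasibility outcomes.** Among the primary outcomes, item 3 covers retention to 12 months with complete datasets, item 6 the time that data collection takes, item 7 a 5-point rating of the treatment, and item 8 the standard deviation for weight, for sizing a later trial. Tertiary qualitative outcomes plans interviews with 12 participants about taking part in the study and the groups. The Discussion adds a second use of the data: examining a range of treatment outcomes, with mediators and moderators.

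**The concern.** The stated question about the secondary measures is whether each one would serve as an outcome in a full trial. Answering it needs evidence on each instrument: whether people completed it, which items they skipped, how long it took, and how its scores varied. The inferential method named answers a different question, namely how scores changed or differed. It also brings in significance tests that the Sample size section rules out.

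The definitive trial has to choose among these measures. Without instrument-level results it could see that the battery as a whole is burdensome or incomplete, but not which questionnaire is responsible, or whether the losses gather at the telephone contacts.

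**Working it through.** **1. Count of measures.** From the three lists in the protocol:
- Obesity and health and wellbeing: King's staging, IPAQ, Mediterranean diet, AUDIT, DEBQ, HADS, and "Weight in kilograms" = 7.
- Costs: CSRI, EQ-5D-5L, ICECAP-A = 3.
- ACT processes: DTS, PHLMS, DDS, PAAQ, FAAQ = 5.

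7 + 3 + 5 = 15. Removing weight and King's staging leaves 13 questionnaires. The two weekly process measures used inside the ACT sessions are part of the intervention and are not counted.

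**2. Numbers available.** The plan recruits 58, allowing for 30% loss. Its evaluable target is not stated, but N/(1 − 0.30) gives 24 → 35, 40 → 58 and 50 → 72 (rounded up), so 58 matches a target of 40. In the other direction, 58 × 0.70 = 40.6, or about 40 people at 12 months and about 20 per arm.

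**3. Planned elements against the stated aim.**

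| Element | Level | What it tells us about one instrument |
|---|---|---|
| ANCOVA | Score | Responsiveness, residual SD; not completion or acceptability |
| Descriptive statistics | Stated for the study population | Nothing explicit |
| Complete case and carried-forward analyses | Handling of missing values | Nothing on where values are missing or why |
| Cost-consequence analysis | Costs and outcomes by arm | Uses the cost measures; does not assess them |
| Item 3, complete datasets | Participant, whole battery | Not separable |
| Item 6, time | Not stated | Depends on how it is recorded |
| Item 7, acceptability | Treatment | Nothing |
| Item 8, SD | Weight | Variability of weight only, for sample size |
| Interviews, n = 12 | Experience of the study and groups | Possible, but questionnaires are not a named topic |

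No row gives completion, missing items or burden by instrument.

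**4. Why a whole-battery figure is not enough (illustration).** The protocol gives no completion rates, so these are assumed. If each of 13 questionnaires is completed independently with probability p, the proportion of attenders with a complete set is p^13:
- p = 0.95: 0.95^13 = 0.51
- p = 0.97: 0.97^13 = 0.67
- p = 0.99: 0.99^13 = 0.88

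A result of 67% would also arise if 12 questionnaires were always completed and one was completed by 67% of people. The two cases call for different decisions, and item 3 cannot tell them apart.

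**5. Would per-instrument figures be informative at this size?** Wilson 95% interval: centre (p + z²/2n)/(1 + z²/n), half-width z√(p(1−p)/n + z²/4n²)/(1 + z²/n), z = 1.96. For assumed completion rates:
- n = 58: 70% → 57 to 80%; 80% → 68 to 88%; 90% → 80 to 95%.
- n = 40: 60% → 45 to 74%; 70% → 55 to 82%; 80% → 65 to 90%; 90% → 77 to 96%.

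With 40 people, an instrument at 90% is separated from one at 60%, but not clearly from one at 80%.

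**6. What the tests could add.** With 20 per arm, SD 1 and two-sided 0.05, a plain two-sample comparison (normal approximation, no gain from baseline adjustment) has power of 35% for a standardised difference of 0.5 and 72% for 0.8. With one independent null test per measure, the chance of at least one significant result is 1 − 0.95^15 = 54%. The effect sizes and independence are assumptions; measures of this kind are likely to be correlated. Significance would therefore be a weak guide to an instrument's worth.

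**The case against.** The strongest reply has four parts.

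- **ANCOVA is not out of place.** An outcome for a trial must be able to change, and the fit supplies a residual SD and the relation to baseline. The Discussion also gives the data a second use, which ANCOVA serves. This stands, and it is why the method should be kept. Responsiveness and variability are, however, only part of suitability and say nothing about acceptability.
- **ANCOVA is not alone.** A reader might infer that it is the only analysis planned. It is not: descriptive statistics, two approaches to missing data, a cost-consequence analysis and interviews are all named. None of them is set at the level of the instrument for this aim.
- **The data will exist.** A reader might infer that the trial cannot say which measures to keep. That goes too far, because completion and missing items can be tabulated later from the forms. Time per questionnaire is different: if it is not noted at collection, it cannot be recovered.
- **Table specifications belong in an SAP.** Also right: the absence of item-level or floor and ceiling tables would be no finding by itself. The point rests on what the protocol fixes, namely the aim, the inferential method, and the definitions of completeness and acceptability.

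A reader might also infer that the full trial will inherit the whole battery, or pick its outcomes by p-value. The protocol says neither.

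**Conclusion.** The concern holds as a mismatch between a stated aim and the method named for it. The secondary measures are there to test the instruments, whereas the inferential analysis tests scores at 0.05, against the protocol's own statement that it will not test hypotheses. Completeness is defined over the battery, acceptability for the treatment, and time at no stated level. There is thus no planned instrument-level basis for keeping or dropping any of the 15 measures; the SD for weight in item 8 is meant for sample size.

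The consequence is an under-answered feasibility question, not a threat to the validity of the randomised comparison, and much of it can be repaired from data already planned. The count of 15 and the two definitions come straight from the protocol. The 67% figure is only an illustration, resting on an assumed 97% independent completion rate. The precision figures rest on assumed completion rates and on about 40 people retained, which follows from the protocol's 30% loss.

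**What to change.** In Data collection and measures and in Statistical data analysis:

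1. Make the main analysis of the secondary measures one per instrument and time point: percent completed among those assessed with a 95% CI, missing items, and SD. Because 3 and 6 months are by telephone and baseline and 12 months face to face, this also shows results by mode, although mode cannot be separated from time.
2. State that item 6 is recorded per questionnaire, at the time of collection.
3. Report ANCOVA between-arm differences as estimates with confidence intervals and drop the significance tests. This also removes the conflict with Sample size.
4. Keep the cost-consequence analysis and the interviews as planned.

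The cost is a different set of tables from data already being collected, plus slightly more recording by the data collector for the timings. No extra participants or visits are needed.

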### *Obesity and health and wellbeing*

The King's Obesity Staging Criteria. This measures the severity of an individual's obesity based on a four-graded set of health-related domains. It can capture health problems related to obesity and health benefits after weight loss.

The International Physical Activity Questionnaire (IPAQ). This measures levels of physical activity.

The Brief Mediterranean Diet Questionnaire. This measures adherence to a Mediterranean diet which is recommended as part of the intervention.

The Alcohol Use Disorders Identification Test (AUDIT). This measures alcohol consumption, drinking behaviours, and alcohol-related problems.

The Dutch Eating Behaviour Questionnaire (DEBQ). This measures eating behaviour in terms of restraint, emotional, and external eating.

The Hospital Anxiety and Depression Scale (HADS). This measures levels of anxiety and depression.

Weight in kilograms.

### *Costs*

The Client Service Receipt Inventory (CSRI). This measures resource use by participants by asking them about their health service use and social service over the last 3 months. Questions relate to healthcare use in both primary care [general practitioner (GP) and community nursing services] and secondary care as well as accident and emergency (A&E) department. Participants will be asked to report the frequency and intensity of their service use.

EQ-5D-5L: This measures health-related quality adjusted life years (QALY). The five attributes of this questionnaire (mobility, self-care, usual activities,

pain/discomfort/anxiety/depression) will be summarised into a single UK-derived preference-based utility score.

ICECAP-A (ICEpop CAPability measure for Adults): This is a measure of capability for the general adult population for use in economic evaluation. It focuses on wellbeing defined in a broader sense than health. The measure covers attributes of wellbeing that were found to be important to adults in the UK.

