**ABSTRACT Background:** Bariatric surgery is an effective treatment for obesity. However, around one in five people experience significant weight regain. In the months following surgery, loss of food as a hedonic reward, increased sensitivity to food-related cues, alcohol use and depression may translate into new obesogenic behaviours which can be targeted in therapy. Acceptance and Commitment Therapy (ACT) teaches acceptance of and defusion from thoughts and feelings which influence behaviour, and commitment to act in line with personal values. We will test whether people who have had bariatric surgery over one year ago find 10 weeks of ACT group therapy an acceptable treatment and whether a larger trial to test whether ACT can improve long-term post-operative outcomes would be feasible. **Methods:** This will be a feasibility randomised controlled trial (RCT) with participants randomised to either ACT or a Usual Care Support Group control. Participants will be recruited at 15-18 months post-surgery and compared at baseline, 3, 6 and 12 months. The trial will provide information about recruitment and characteristics of the proposed outcome measures to inform a definitive RCT. **Conclusions:** Trials big enough to determine whether a treatment approach works are costly, so this small study will help determine whether the methods used, such as how people are recruited, allocated to groups, and how data are collected, are likely to work on a bigger scale. This project is the first step in testing whether ACT can help people who have had bariatric surgery. **Trial Registration:** Researchregistry.com, UIN: 3959 (date registered: 10 April 2018); ISRCTN registry ID: ISRCTN52074801.

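### Three-month service-use recall at 3, 6 and 12 months leaves months 6–9 uncollected, yet total costs per person are to be compared

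*Protocol*

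**What the plan says.** In the protocol's Costs section, the CSRI measures resource use "by asking them about their health service use and social service over the last 3 months". No other recall period is given for any time point.

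The schedule is set in the section on data collection, which reads: "A standardised battery of measures will be completed at baseline, three, six and 12 month follow up, except for weight". The only other measure exempted is the King's staging of obesity; those two are taken at baseline and 12 months only. The CSRI is not exempted, so it follows the four-point schedule. The same section adds that "three and six month follow up data will be collected via telephone", while baseline and 12 months are face to face. No contact at month 9 is mentioned.

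Under Statistical data analysis, "A cost-consequence analysis (CCA) will be carried out from a National Health Service (NHS) perspective". On service use it says: "Total costs of the individuals in the two groups will be compared and estimated by multiplying the resource use with the unit costs". The unit costs meant are those for health and social care. Costs are then to be shown next to whatever benefits the trial finds. Delivery of the groups is handled apart from the CSRI: "The intervention costs will be calculated based on the activities involved in delivering the programme".

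**The concern.** A fixed 3-month look-back gives continuous coverage only if the visits are no more than 3 months apart. Here the last two are 6 months apart. A participant admitted, referred on or re-operated seven months after baseline would not be asked about it at month 6, when it had not yet happened, or at month 12, when it lay outside the window.

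Two things are at stake. First, a per-person figure described as a total would leave out part of follow-up while standing beside outcomes such as weight and obesity stage, which run from baseline to 12 months. Second, the protocol collects its secondary measures to see whether the instruments suit a full trial. A schedule that leaves a quarter of the year unobserved could be carried unchanged into the definitive economic evaluation. The Introduction and Discussion cite the cost of re-operation and weight regain as part of the case for the therapy, and re-operations are the kind of infrequent, expensive event that a gap of this sort can miss.

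**Working it through.** The protocol states no coverage figure to reproduce, so the check is a count of months.

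**Inputs**
- Recall window: 3 months (Costs).
- Administration times: months 0, 3, 6 and 12 (Data collection and measures). The Abstract gives the same times: "Participants will be recruited at 15-18 months post-surgery and compared at baseline, 3, 6 and 12 months".
- Follow-up: 12 months after baseline (same places).

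**Coverage.** Each administration at time *t* covers the interval from *t* − 3 to *t*.

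| CSRI given at | Months covered | Follow-up months covered |
|---|---|---|
| Baseline | −3 to 0 | 0 (before randomisation) |
| Month 3 | 0 to 3 | 3 |
| Month 6 | 3 to 6 | 3 |
| Month 12 | 9 to 12 | 3 |

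Covered: 3 + 3 + 3 = 9 of 12 months (75%). Not covered: months 6 to 9, which is 3 of 12 (25%).

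**Effect on cost.** Let *S* be the true 12-month service cost per person and *D* the delivery cost of the group. *D* is calculated from programme activities, and both groups run for 10 weeks from their start, so *D* does not depend on the CSRI.
- If use is even over time, the CSRI captures 0.75 × *S*, so service cost is understated by 25%.
- The combined cost is understated by 0.25 × *S* / (*S* + *D*). This is below 25% whenever *D* is above zero. The protocol gives neither *S* nor *D*, so no single figure can be put on it.
- If use is uneven, the loss is whatever share of *S* falls in months 6–9, which is not known.

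**Illustration of a single large event.** The Introduction gives £10,000 per re-operation. With 58 participants allocated equally there are 29 per arm, and one unrecorded re-operation moves that arm's mean by 10,000 / 29 ≈ £345. At the 30% loss to follow-up assumed under Sample size, 58 × 0.7 = 40.6 remain, about 20 per arm, and the shift is 10,000 / 20.3 ≈ £493 (£500 with exactly 20). No event rate is given, so this shows sensitivity to one event and is not an expected bias.

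**Coverage after a change.** A 6-month window at month 12 gives 3 + 3 + 6 = 12 months. An added 3-month CSRI at month 9 gives 3 + 3 + 3 + 3 = 12 months. Either closes the gap.

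**The case against.** The strongest reply is that the protocol never says costs are annual. A total could mean a sum over types of service within the observed windows, and outcomes are also measured at 3 and 6 months. This stands: the 12-month horizon is inferred from the follow-up schedule, so this is a gap relative to a likely target and not a contradiction in the text.

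A reader might go further and infer that each arm's total cost is understated by a quarter. The document does not support that, because delivery costs are calculated separately and are not lost. The 25% applies to CSRI-derived costs only, and only under even use. A reader might also infer a bias towards one arm. The windows are the same in both arms, so nothing in the design favours either; what is lost is any difference in use that arises in months 6–9.

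It can also be said that the stakes are low, since costs are secondary in a feasibility study and completion of the CSRI can be judged from four administrations. That limits the consequence but does not remove the gap. Whether a schedule suited to annual costing can be completed is something this study could usefully learn.

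Finally, an analysis plan not shown here might interpolate between the adjacent windows, and the planned sensitivity analyses offer a place for that. Interpolation is reasonable for frequent, steady items such as general practice contacts. It does not work for rare, large ones, and no analysis plan can observe what was not asked. The recall window and the visit schedule are both fixed in the protocol, so this is not a matter left to later documentation.

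**Conclusion.** The gap is real and follows directly from two statements in the protocol: self-reported service use in months 6–9 after baseline, 3 of 12 follow-up months, is not collected. If the intended horizon is the 12-month follow-up, CSRI-derived service costs are understated by about 25% under even use. The understatement of combined cost is smaller by an amount the protocol does not allow one to calculate. Rare expensive events in the gap are lost altogether.

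The conclusion rests on three assumptions: that the 3-month window applies at every administration, as printed; that the cost horizon is 12 months, which is inferred; and, for the 25%, that use is level over time. The consequence is moderate because costs are a secondary outcome of a feasibility trial. The correction is cheap and worth making before the schedule is reused in a larger trial.

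**What to change.** At the 12-month visit, word the CSRI to cover the period since the 6-month contact (6 months), and keep 3 months at baseline, month 3 and month 6. State the cost horizon in the analysis section as the 12 months from baseline.

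The cost is one changed line on one form at a visit that already takes place face to face. The downsides are somewhat more recall error over the longer period and a recall length that differs between time points. Because the time needed to collect data is one of the trial's feasibility measures, the burden of the longer window would be assessed in the course of the study. A 3-month CSRI by telephone at month 9 would keep one recall length but adds a contact. Checking admissions and operations against hospital records would be extra work and is not needed to close the gap.

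If the schedule is to stay as it is, say that service costs cover months 0–6 and 9–12 only, do not describe them as total costs, and state how months 6–9 are treated if an annual figure is wanted.
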